#### 2.4.4 Discontinuation criteria, adherence and concomitant therapy

Long-term medications for the treatment of underlying diseases, such as high blood pressure, are allowed. Other symptomatic treatments, such as NSAIDs, may be used if the investigators judge that they will not interfere with the assessment of the study drug. We strictly prohibit glucocorticoids, either oral or topical. All concomitant medications should be recorded in the case report form (CRF).

The trial intervention should be stopped in the following circumstances: if serious adverse events (SAEs) occur; if the patient’s condition deteriorates drastically during the trial and it cannot be ruled out that the change is related to the trial, the study should be terminated, and the necessary treatment measures should be taken for the patient; and if patients withdraw their consent.

The duration of the intervention phase and subsequent follow-up in this study are notably extensive, particularly for participants who are asymptomatic. To improve medication adherence, our approaches encompass the following aspects:

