#### 2.5.4 Safety assessment

Safety assessment includes complete blood count (CBC), urinalysis (UA), liver function tests (LFTs) (AST and ALT), renal function tests (RFTs) (creatinine and urea), electrocardiogram (ECG), chest X-ray, and adverse events (AEs),

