### 2.6 Participant timeline

Fifty-two weeks of medical intervention will be followed by another 52 weeks of observation, for a total of 104 weeks. The time points for the measurements are as follows: screening (0 days), 4 ± 3 days, 12 ± 5 days, 24 ± 5 days, 52 ± 5 days, 78 ± 5 days and 104 ± 5 days. During the trial and follow-up, participants will be observed and evaluated via clinical and/or imaging examinations.

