#### 2.9.2 Statistical methods

Data analysis will be conducted by statisticians who are independent of the research team. All analyses are performed via the SPSS software (IBM SPSS Inc., Armonk, NY, USA). An intent-to-treat analysis will be carried out for participants who receive treatment at least once. Missing data will be imputed in accordance with the principle of multiple imputations. Continuous variables will be imputed using linear regression models, while categorical variables will be imputed using logistic regression models. Multiple imputation was performed with a user-defined number of MCMC (Markov Chain Monte Carlo) iterations. Per-protocol analysis is limited to participants who strictly adhere to the protocol and complete the trial. All the statistical tests are 2-sided, and differences are considered statistically significant at *P* values less than 0.05.

The safety dataset will also include all patients who received ≥1 dose of the intervention. The primary outcomes will be compared between the two groups via the log-rank test and the Kaplan–Meier method, and superiority will be considered with a 95% confidence interval. The secondary outcomes will be presented as frequencies, means, standard deviations (SDs), medians and ranges. To determine treatment effects, changes in the above outcomes from baseline will be analyzed via ANOVA. Group effects and influencing factors will be analyzed via analysis of covariance or a logistic regression model with covariates including sex, age, concomitant medication and measurements at baseline. Subgroup analyses will not be performed to avoid insufficient statistical power because of the small sample size. Safety will be evaluated through tabulations of AEs and coded based on the Chinese version of the Medical Dictionary for Regulatory Activities (MedDRA). Safety data will be presented with descriptive statistics at baseline, 52 weeks and 104 weeks for each group.

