**FIGURE 2 F2:**
[figure not shown]
Trial flowchart.

**TABLE 2 T2:** Time schedule and measurements.

Assessment	Visit 1	Visit 2	Visit 3	Visit 4	Visit 5	Visit 6	Visit 7
	Enrollment	4^th^ w	12^th^ w	24^th^ w	52^th^ w	78^th^ w	104^th^ w
Demographic data	×						
Family history	×						
Medical history	×						
Physical examination	×	×	×	×	×	×	×
Vital signs	×	×	×	×	×	×	×
Disease activity	×	×	×	×	×	×	×
Morning stiffness	×	×	×	×	×	×	×
TJC28	×	×	×	×	×	×	×
SJC28	×	×	×	×	×	×	×
HAQ	×	×	×	×	×	×	×
VAS	×	×	×	×	×	×	×
PtGA	×	×	×	×	×	×	×
PGA	×	×	×	×	×	×	×
GQOLI-74	×			×	×	×	×
anti-CCP	×		×	×	×	×	×
RF	×	×	×	×	×	×	×
hs-CRP	×	×	×	×	×	×	×
ESR	×	×	×	×	×	×	×
DAS28-CRP	×	×	×	×	×	×	×
CBC	×	×	×	×	×	×	×
UA	×	×	×	×	×	×	×
LFTs	×	×	×	×	×	×	×
RFTs	×	×	×	×	×	×	×
ECG	×				×	×	×
Chest radiography	×				×	×	×
DR of the joints	×				×	×	×
Ultrasound	×		×	×	×	×	×
Concomitant medication	< — — — — — — — — — — — — — — — — — — — — — — — — — — >						
Adverse events	< — — — — — — — — — — — — — — — — — — — — — — — — — — >						
Concomitant medications	< — — — — — — — — — — — — — — — — — — — — — — — — — — >						

TJC28, 28-tender joint count; SJC, 28-swollen joint count; HAQ, health assessment questionnaire; VAS, visual analog scale; PtGA, patient’s global assessment; PGA, physician’s global assessment; GQOLI-74, generic quality of life inventory-74; anti-CCP, anti-cyclic citrullinated peptide; RF, rheumatoid factor; hs-CRP, high-sensitivity C-reactive protein; ESR, erythrocyte sedimentation rate; DAS28-CRP, disease activity score in 28 joints-C-reactive protein; CBC, complete blood count; UA, urinalysis; LFTs, liver function tests; RFTs, renal function tests; ECG, electrocardiogram; DR, digital radiography.

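### Laboratory and vital-sign values are to be summarised at two of six post-baseline visits, omitting three of the four in the treatment year

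*Protocol article*

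**What the plan says.** Section 2.5.4 defines the safety measures: "Safety assessment includes complete blood count (CBC), urinalysis (UA), liver function tests (LFTs) (AST and ALT" and further items, namely renal tests, electrocardiogram, chest X-ray and adverse events.

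Table 2 ("Time schedule and measurements") sets seven visits: "Enrollment 4^th^ w 12^th^ w 24^th^ w 52^th^ w 78^th^ w 104^th^ w". Blood count, urinalysis, liver tests, renal tests and vital signs are marked at all seven. Electrocardiogram and chest radiography are marked at enrollment and weeks 52, 78 and 104.

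Section 2.6 gives the periods: "Fifty-two weeks of medical intervention will be followed by another 52 weeks of observation, for a total of 104 weeks".

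Section 2.9.2 makes three statements about safety analysis. The population: "The safety dataset will also include all patients who received ≥1 dose of the intervention". The main evaluation: "Safety will be evaluated through tabulations of AEs", coded in MedDRA. The time points: "Safety data will be presented with descriptive statistics at baseline, 52 weeks and 104 weeks for each group".

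Section 2.9.3 has adverse events recorded throughout the study with their time of occurrence, severity, causality, action taken and outcome. It also counts clinically significant abnormal blood, urine, liver, kidney and electrocardiogram findings as adverse events.

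**The concern.** The article does not leave the time points for descriptive safety data to a later document. It names three of the seven visits at which laboratory tests are done. Only one of the two post-baseline time points falls within the treatment period, at its very end. The other comes a year after planned treatment ends.

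The visits left out are those closest to the start of treatment. A rise in liver enzymes at week 4 or 12 that has settled by week 52 would leave no trace in a table of values at weeks 52 and 104. Someone who left the study at week 20 would contribute a baseline value and nothing afterwards. At stake is the description of early tolerability of a year-long product in people who do not have RA. A trial whose stated aim is feasibility should report that well.

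**Working it through.** No sample size, power or event figure bears on this point, so there is no figure of the plan to reproduce. The check is a count of visits in Table 2 against the time points in 2.9.2, followed by a trace of what the adverse event route captures.

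**Step 1: visits against time points.** This applies to blood count, urinalysis, liver tests, renal tests and vital signs.

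| Visit (Table 2) | Period | Measured | Time point named in 2.9.2 |
|---|---|---|---|
| Enrollment | baseline | yes | yes |
| Week 4 | treatment | yes | no |
| Week 12 | treatment | yes | no |
| Week 24 | treatment | yes | no |
| Week 52 | end of treatment | yes | yes |
| Week 78 | observation | yes | no |
| Week 104 | end of observation | yes | yes |

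- Post-baseline visits: 6. Summarised: 2. Omitted: 6 − 2 = 4, or 4/6 = 67%.
- Treatment-year visits, counting week 52: 4. Summarised: 1. Omitted: 4 − 1 = 3, or 3/4 = 75%.
- Electrocardiogram and chest radiography: 3 post-baseline visits, 2 summarised. Only week 78 is omitted, so the point hardly touches them.

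Section 2.6 lists the visit times in days, whereas Table 2 gives weeks. The count follows Table 2 and does not depend on the unit.

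**Step 2: how many participants could lack a later value.** Section 2.7 plans 30 per group plus 20% for dropout: 30 × 1.2 = 36 per group, 72 in all. The allowance is 72 − 60 = 12 participants, or 12/72 = 17%. The article does not say when they would leave. Between 0 and about 12 could therefore lack an observed week-52 value on the plan's own figures, and up to about 12 a week-104 value.

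**Step 3: what each route captures.**

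| Event | Adverse event tables | Value summaries as stated |
|---|---|---|
| Clinically significant laboratory abnormality at week 4, 12 or 24 | yes | no, unless still present at week 52 |
| Transient change not judged clinically significant | no | no |
| Small shift across a whole arm at weeks 4 to 24, gone by week 52 | no | no |
| Laboratory values of someone who left before week 52 | only if judged clinically significant | baseline only |

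The second, third and fourth rows are the gap. Section 2.9.3 gives no numerical threshold for clinical significance, so the boundary rests on the investigator. Its list of abnormal findings does not name vital signs. Section 2.5.4 does not list them as a safety measure either, although Table 2 collects them at every visit.

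**The case against.** The strongest reply is that adverse events, not laboratory means, are the main safety analysis. They are collected continuously and tabulated without restriction to any visit, in everyone with at least one dose. A liver enzyme rise serious enough to end treatment would be judged clinically significant, and so recorded with its onset and the action taken. This stands. A reader might infer from the three time points that early toxicity and early stoppers vanish from the safety tables altogether. The documents do not support that, because both remain in the adverse event tabulation.

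Second, section 2.4.4 says only that "The trial intervention should be stopped in the following circumstances: if serious adverse events (SAEs) occur", among other circumstances. It does not say that such participants miss later visits, and some may be seen at week 52. This also stands. The week-52 table cannot be assumed to hold only those who tolerated a year of treatment. But anyone who does attend after stopping contributes an off-treatment value at week 52, which is no substitute for the value at the time of the change.

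Third, weeks 52 and 104 are the ends of the two periods, a coherent choice for a short article, and the sentence does not say that no other safety output will be made. Worst values and shift tables are often set out in an analysis plan, and one that is not shown may contain them. This keeps the point minor but does not remove it: the article names specific time points, and the natural reading is that they are a selection.

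**Conclusion.** The point holds in a limited form. As stated, the descriptive summaries of laboratory and vital-sign values cover two of six post-baseline visits and one of the four in the treatment year. They would not show early changes that are transient or below the investigator's threshold. Nor would they show the observed values of participants who left before week 52, who number at most about 12 of 72 on the plan's dropout allowance.

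This rests on two assumptions: that the named time points are the full set for value summaries, and that vital signs count as safety data. It does not show that clinically significant harm would go unreported, and the documents give no toxicity rate from which to estimate missed cases. It is a minor weakness of reporting.

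**What to change.** Amend the sentence on descriptive safety data in 2.9.2 so that:

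- laboratory and vital-sign data are summarised by arm at every scheduled visit in the safety set, with the number of participants observed at each visit;
- each participant's worst on-treatment value and shift from baseline are tabulated by arm, including those who stopped early;
- the adverse event tabulation stays as planned.

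If an analysis plan already provides this, it is enough to bring the article's sentence into line with it. The cost is a few extra tables. The data are already scheduled for collection, and no visit, test, sample size or clinical procedure changes.

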#### 2.9.3 Monitoring

Any adverse events (AEs) that occur during the study period will be reported to the investigators and recorded in the CRFs. In addition to participant self-reports, abnormal laboratory findings, including routine blood tests, urine tests, liver function tests, kidney function tests and pathological electrocardiograms with clinical significance, will be recorded as AEs. AE details, including the time of occurrence, severity, causality with the intervention, actions taken, and AE outcomes, will be observed and assessed. Causalities between AEs and the FA granules will be assessed according to the WHO Uppsala Monitoring Centre System for Standardized Case Causality Assessment^2^. Any severe AEs or serious adverse drug reactions will be addressed promptly to ensure patient safety and will be reported to the principal investigator and the hospital ethics committee in a timely manner.

The trial flowchart is shown in Figure 2, and the schedules and measurements for the participants are listed in Table 2.

**FIGURE 2 F2:**
[figure not shown]
Trial flowchart.

**TABLE 2 T2:** Time schedule and measurements.

Assessment	Visit 1	Visit 2	Visit 3	Visit 4	Visit 5	Visit 6	Visit 7
	Enrollment	4^th^ w	12^th^ w	24^th^ w	52^th^ w	78^th^ w	104^th^ w
Demographic data	×						
Family history	×						
Medical history	×						
Physical examination	×	×	×	×	×	×	×
Vital signs	×	×	×	×	×	×	×
Disease activity	×	×	×	×	×	×	×
Morning stiffness	×	×	×	×	×	×	×
TJC28	×	×	×	×	×	×	×
SJC28	×	×	×	×	×	×	×
HAQ	×	×	×	×	×	×	×
VAS	×	×	×	×	×	×	×
PtGA	×	×	×	×	×	×	×
PGA	×	×	×	×	×	×	×
GQOLI-74	×			×	×	×	×
anti-CCP	×		×	×	×	×	×
RF	×	×	×	×	×	×	×
hs-CRP	×	×	×	×	×	×	×
ESR	×	×	×	×	×	×	×
DAS28-CRP	×	×	×	×	×	×	×
CBC	×	×	×	×	×	×	×
UA	×	×	×	×	×	×	×
LFTs	×	×	×	×	×	×	×
RFTs	×	×	×	×	×	×	×
ECG	×				×	×	×
Chest radiography	×				×	×	×
DR of the joints	×				×	×	×
Ultrasound	×		×	×	×	×	×
Concomitant medication	< — — — — — — — — — — — — — — — — — — — — — — — — — — >						
Adverse events	< — — — — — — — — — — — — — — — — — — — — — — — — — — >						
Concomitant medications	< — — — — — — — — — — — — — — — — — — — — — — — — — — >						

TJC28, 28-tender joint count; SJC, 28-swollen joint count; HAQ, health assessment questionnaire; VAS, visual analog scale; PtGA, patient’s global assessment; PGA, physician’s global assessment; GQOLI-74, generic quality of life inventory-74; anti-CCP, anti-cyclic citrullinated peptide; RF, rheumatoid factor; hs-CRP, high-sensitivity C-reactive protein; ESR, erythrocyte sedimentation rate; DAS28-CRP, disease activity score in 28 joints-C-reactive protein; CBC, complete blood count; UA, urinalysis; LFTs, liver function tests; RFTs, renal function tests; ECG, electrocardiogram; DR, digital radiography.

## 3 Biobank

Biological samples, including blood, urine and stool samples, will be collected from study participants at each observation time point for future studies to investigate biomarkers for RA prevention.

## 4 Discussion

Although previous studies have tested the use of DMARDs to delay the onset of RA (37, 38), there is also a growing need for clinical evidence for TCM.

However, this trial has several potential limitations. It is a small-scale pilot trial, and therefore, the results may not be conclusive or sufficiently generalizable. Nevertheless, any significant differences or trends in the efficacy of FA at the endpoints of this trial will provide seminal evidence for the search for RA prevention, and even neutral results will be important revelations to the community. RA is a serious global rheumatic disease that affects many people both physically and mentally.

With the rapid advances in science and medicine in recent years, remission is no longer the only goal to meet the needs of RA patients. Medical care and management strategies for at-risk individuals are becoming a priority for clinicians and researchers. This trial can provide high-quality data and hopefully suggest a new therapy to prevent rheumatoid arthritis.

## 5 Study status

This study is ongoing and currently in the patient recruitment phase.
